#### Mediation

We also aim to examine whether changes in various social cognitive dimensions mediate the potential increase in social functioning. In order to test this mediational model, we will carry out a multi-mediator analysis [77]. This allows for a parallel testing of the indirect effects of several social cognitive dimensions, namely: theory of mind, complexity of representations, affect-tone of relationships, capacity for emotional investment and understanding of social causality (Fig. 1).

**Fig. 1 Fig1:**
[figure not shown]
Theoretical model of the effect of treatment condition on social functioning, mediated by social cognition

#### Multilevel analysis

Social stress reactivity is measured by ESM. This method generates data with a multilevel structure because there are multiple measurements per day for 5 days at a time for each patient. Since observations within patients tend to be more similar than observations from different patients, they are not independent. This necessitates a different (i.e., multilevel) analysis than the one used for the other outcome measures. Similar to Myin-Germeys and colleagues [78], differences in social stress reactivity between groups will be analyzed using mixed-effects regression models with treatment condition, the amount of stress during social situations, and their interaction term as independent variables, and positive and negative affect as dependent variables. The model will include random intercepts and random slopes for the stress predictor at the patient level, which allows for differences in overall levels of positive and negative affect across patients and for differences in the strength of the relationship between stress and these outcomes.

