### Covariates

Certain potential effect modifiers will be taken into account. First, adverse childhood experiences such as neglect or physical, psychological, and sexual abuse have been associated with social dysfunction later in life [40]. Second, personality organization (PO) has been shown to impact psychotherapy treatment response [41] and the level of social cognition [42]. Five levels of personality organization (PO) are identified, each characterized by different levels of anxiety tolerance and different capacities for impulse inhibition or ‘control’: Neurotic PO (good anxiety tolerance, over-control); Borderline PO (moderate to poor anxiety tolerance, differing levels of control); Narcissistic Borderline PO (good anxiety tolerance, undercontrol); Latent Psychotic PO (moderate anxiety tolerance, weak control); and Manifest Psychotic PO (poor anxiety tolerance, weak control). Third, the awareness of bodily sensations has been regarded as the first level of emotional awareness [43], which is an essential part of social cognition [44]. Psychopathology usually is accompanied by (vague) physical complaints, called “somatization”. A failure to report physical complaints while suffering (severe) psychopathology may be indicative of an absence of bodily awareness and therefore an impaired social cognitive capacity. Fourth, medication use can affect social functioning in patients with NAPD, therefore the type of medication is registered and adherence to medication is measured. Fifth, MBT attendance is taken into account, because it is expected that those who attend more sessions will profit more. Sixth, baseline measurements of the outcome variables will be accounted for. Seventh, the duration of illness, because of its negative impact on functioning; and eighth, adherence to the MBT model by therapists, because it is likely to influence treatment outcome.

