## Measurements and instruments

There are four moments of assessment over the course of 2 years. The baseline assessment takes place before MBT-P is started. Furthermore, there will be an assessment after 9 months (halfway MBT-P), after 18 months (directly after MBT-P has ended), and after 24 months (6 months after MBT-P has ended). See Table 1 for the specific instruments that are used at each assessment.

**Table 1 Tab1:** Overview of the different instruments at each measurement moment

	Intake	T0: Baseline measurement (0 months)	T1: Halfway Measurement (9 months)	T3: End of Treatment (18 months)	T4: Follow-up (24 months)
CASH	X				
SFS		X		X	X
TAT		X		X	X
ESM		X	X	X	X
HT		X		X	X
MANSA		X		X	X
MAQ		X	X	X	X
DSFM		X			
PANSS		X		X	X
GDQ		X			
CECA		X			
GAF		X		X	X

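### The social stress reactivity model names no target assessment and has no wave or baseline term, although ESM data come from four assessments, one of them before treatment

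*Protocol article*

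**What the plan says.** The Multilevel analysis section takes social stress reactivity out of the analysis used for the other outcomes: "This necessitates a different (i.e., multilevel) analysis than the one used for the other outcome measures". The reason given is that observations within a patient are not independent. It describes the data by saying that "there are multiple measurements per day for 5 days at a time for each patient". The fixed effects are those of "mixed-effects regression models with treatment condition, the amount of stress during social situations, and their interaction term as independent variables", with positive and negative affect as dependent variables. For the random part, "The model will include random intercepts and random slopes for the stress predictor at the patient level".

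Three other places bear on this:

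- Measurements and instruments: "There are four moments of assessment over the course of 2 years". Table 1 marks ESM at all four (0, 9, 18 and 24 months), and "The baseline assessment takes place before MBT-P is started".
- Covariates: "Sixth, baseline measurements of the outcome variables will be accounted for".
- Main effect: post-treatment social functioning is analysed by ANCOVA with its baseline as covariate, and similar analyses are promised for a list of secondary outcomes. Social stress reactivity is not on that list, so the Multilevel analysis section is the only analysis stated for it.

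**The concern.** The hypothesis, in Secondary research aims, is causal: MBT-P should reduce aversive emotional reactions to social stress. With four ESM waves, the listed terms can be fitted in more than one way, and the text does not choose.

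Pooling every beep from every wave gives one treatment-by-stress coefficient that mixes pre-treatment, mid-treatment, end-of-treatment and follow-up reactivity. Because the pre-treatment wave cannot carry a treatment effect, the coefficient is pulled towards zero. Using one post-treatment wave avoids this, but baseline reactivity, which has been collected and is likely to be correlated with later reactivity, then goes unused.

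The readings target different quantities. If the choice stays open until the data are in, the wave or waves analysed can be chosen after the results are seen.

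**Working it through.** The protocol gives no figure for the ESM model, so there is none to reproduce. Its sample-size figure concerns social functioning and is not in question: a two-sided t-test with d = 0.7 needs 34 per arm, 68 in total, and (1 − 0.4²) × 68 = 57.1, rounded up to 58.

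**Step 1: what pooling estimates.** Let D be the full effect of MBT-P on the stress slope, reached at 18 months and held at 24. Assume equal numbers of beeps per wave; the protocol gives no beep counts by wave. The pooled interaction is then the mean of the four wave-specific effects:

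- full effect by 9 months: (0 + 1 + 1 + 1)/4 = 0.75D
- half the effect by 9 months: (0 + 0.5 + 1 + 1)/4 = 0.625D
- no effect by 9 months: (0 + 0 + 1 + 1)/4 = 0.50D

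The loss is 25% to 50%.

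**Step 2: precision.** The documents give no variances for reactivity, so these values are assumptions for illustration: D = 0.10 (a reduction), between-patient slope SD 0.15, wave-to-wave SD within patient 0.10, and SE 0.06 for estimating one patient's slope at one wave. The planned 40 per arm is used. The variance components are 0.0225, 0.0100 and 0.0036.

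- One wave: variance 0.0225 + 0.0136 = 0.0361; SE of the arm difference √(0.0361 × 2/40) = 0.0425.
- Four waves pooled: variance 0.0225 + 0.0136/4 = 0.0259; SE 0.0360.
- 18 months adjusted for baseline: correlation 0.0225/0.0361 = 0.623; residual variance 0.0361 × (1 − 0.623²) = 0.0221; SE 0.0332.
- Change from 0 to 18 months, baseline unconstrained: variance 2 × 0.0136 = 0.0272; SE 0.0369.

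A simulation of per-patient slopes (4,000 replicates per effect pattern) gave:

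| Analysis | Mean estimate (true −0.10) | Power |
|---|---|---|
| Listed model, four waves pooled, full effect by 9 months | −0.075 | 0.54 |
| Listed model, four waves pooled, half effect by 9 months | −0.063 | 0.40 |
| Listed model, 18 months only | −0.10 | about 0.65 |
| 18 months, baseline reactivity as covariate | −0.10 | about 0.84 |
| Treatment by stress by wave, 0 to 18 months, baseline unconstrained | −0.10 | about 0.77 |

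The no-effect-by-9-months pattern was not simulated. From the SE above, 0.050/0.0360 = 1.39, so power is about Φ(1.39 − 1.96) = 0.28.

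**Step 3: false positives.** With no effect at any wave, rejection at the 5% level lay between 0.046 and 0.052 for all four analyses.

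**Step 4: random effects once a wave contrast is added.** The plan has "random intercepts and random slopes for the stress predictor at the patient level" only. Treatment does not vary within a patient, so for the two-way interaction as listed this does little harm. A 0-to-18-month contrast, however, rests on within-patient change. Under the values above, leaving out wave-to-wave slope variance would shrink its SE to about √(0.0036/0.0136) = 0.51 of the right size. The nominal 5% error would then be roughly P(|Z| > 1.96 × 0.51) ≈ 0.31. This figure is approximate, but it shows why a wave term needs a patient-by-wave random slope beside it.

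**The case against.** The best reply is that nothing in the text says the four waves will be pooled. The description of several beeps a day over five days fits one ESM period, so a single post-treatment wave is at least as natural a reading. On that reading the arms are randomised, the two-way interaction is an unbiased estimate of the MBT-P effect on reactivity, and chance baseline differences are covered by its standard error. The Covariates section also promises baseline adjustment without exception, and the Multilevel analysis section separates ESM because of non-independence, not in order to abandon that promise. A condensed article may leave such detail to a fuller plan.

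Much of this stands. A reader might infer that the model cannot estimate the treatment effect on reactivity, or that it risks a false positive. The documents support neither: the first holds only if the pre-treatment wave is pooled in, and step 3 shows no inflation. Nor does the text contradict the baseline commitment; it fails to carry it into the model. A reader might also suppose that the model was borrowed from a cross-sectional comparison, but the protocol says only that it resembles a cited study's and does not describe that study's design.

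What does not stand is that this is mere missing detail. The section lists its fixed and random effects explicitly, it is the only analysis given for this outcome, and the list falls short on either reading. The comparison of t0 with t2 under Trial design/setting covers social functioning only, so it does not settle the wave for ESM.

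**Conclusion.** The point holds as a cheap improvement to one secondary outcome. The stated model leaves the target assessment open and omits both wave and baseline. Its cost depends on the reading: a 25% to 50% dilution towards zero if all four waves are pooled, or no bias but a loss of precision if 18 months stands alone (power about 0.65 against 0.84 with baseline adjustment).

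The dilution figures rest on equal beeps per wave and on an effect that is full at 18 and 24 months. The power figures rest wholly on assumed variances and show direction and rough order only. The worst case is a missed effect, not a spurious one.

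**What to change.** Name 18 months as the target assessment for social stress reactivity. State it in months, because Table 1 labels that visit T3 while Trial design/setting calls the post-treatment assessment t2. Then choose one of two models:

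1. **18-month wave with baseline adjustment.** Keep the listed model, fit it to the 18-month beeps, and add each patient's baseline reactivity as covariate, in line with the Covariates and Main effect sections. It should also enter in interaction with stress; a main effect alone adjusts the level of affect, not the slope.
2. **All waves.** Fit treatment by stress by wave, with arm differences at baseline constrained to zero, random stress slopes at patient and patient-by-wave level, and the 18-month contrast as the test. The constraint recovers the precision that a plain change contrast gives up.

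A day-level random intercept and person-mean-centring of the stress score are optional refinements.

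The cost is a few sentences and slightly more complex code; Table 1 already provides the data. The three-way model may have convergence problems: a small mixed-model check with 30 replicates gave convergence warnings. If that is a worry, the first option is simpler.

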## Discussion

There is evidence that MBT improves, among others, social functioning and interpersonal distress in patients with BPD (e.g. [24, 79]) and that these effects remain at follow-up [80]. Given the similarities in both origins and symptoms of BPD and NAPD, it has previously been suggested that MBT could be a useful treatment for NAPD [20, 33]. This randomized controlled trial, will be the first to examine the effectiveness of MBT as an adjunct therapy for patients with NAPD. Furthermore, we aim to determine a possible mechanism of change by examining social cognitive capacity as a possible mediator. By measuring social cognitive capacity with two instruments, covering a total of five dimensions, we mean to do justice to its complexity.

## Abbreviations

(Z)MLK, Abbreviation for the Dutch term ‘(zeer) moeilijk lerende kinderen’ meaning: children with (severe) learning disabilities; BPD, borderline personality disorder; CASH, comprehensive assesment of symptoms and history; CBT, cognitive behavioral therapy; CECA, childhood experiences of care and abuse; DSFM, Dutch short form of the Minnesota Multiphasic personality inventory; ESM, experience sampling method; GAF, global assessment of functioning; GDQ, general demographic questionnaire; HT, hinting task; ITT, Intention to treat; MANSA, Manchester short assessment of quality of life; MAQ, medication adherence questionnaire; MBT, mentalization-based treatment (for borderline personality disorder); MBT-P, mentalization based treatment for psychotic disorders; MCMC, markov chain monte carlo; MI, multiple imputation; MMRM, mixed model for repeated measures; MREC/METC, medical research ethics committee (MREC); in Dutch: medisch ethische toetsing commissie (METC); NAPD, nonaffective psychotic disorder; PANSS, positive and negative syndrome scale; PO, personality organization; SCORS, social cognition and object relations system; SFS, social functioning scale; TAT, thematic apperception test; TAU, treatment as usual
